**Methods:**

A Phase II pilot randomised clinical trial with concealed allocation, blinded measurement, and intention-to-treat analyses will be carried out. The inclusion criteria will be individuals diagnosed with stroke, in the acute or subacute phase, with mild walking disability, sedentary, and no significant language impairment. The participants will be randomly allocated to the experimental or control group. The experimental group will receive six sessions of a home-based self-management program based on behaviour change techniques through the Social-Cognitive Theory and Control Theory over 11 weeks. The control group will receive one session of education about stroke (regarding the importance of practising physical activity after a stroke) and usual care. A total of 24 participants will be recruited. The primary outcome will be physical activity, measured through steps taken per day by an activity monitor (Actigraph wGT3X-BT, Pensacola, FL, USA). The mean of daily steps will be analysed to compare groups after intervention. Secondary outcomes will be cardiovascular risk (body mass index, waist circumference, and blood pressure), depressive symptoms (Geriatric Depression Scale), walking ability (6-Minute Walk Test and 10-Meter Walk Test), exercise self-efficacy (Self-Efficacy for Exercise scale), social participation (Stroke Impact Scale) and quality of life (EuroQual-5D). Two-way analyses of variance will be implemented for all parametric outcomes, and the Kruskal–Wallis test for non-parametric outcomes will be used to determine the statistical significance of the between-group differences and reported as mean differences between groups (95% CI). All analyses will be conducted intention-to-treat. All outcomes will be measured at baseline (Week 0), post-intervention (Week 12), and follow-up (Week 24). This pilot clinical trial was registered online at Clinical Trials under number NCT05461976 on 4^th^ April 2022.

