### Sample size estimate

The present study is a Phase II pilot clinical trial and a specific intervention in a particular sample [sedentary individuals (> 5,000 steps/day) and with mild walking disability (gait speed ≥ 0.8 m/s] will be developed. So, data from the mean and standard deviation required to produce a sample size are unavailable in the literature. So, in this case, a formal sample size calculation will not be undertaken. To estimate the number of participants required in the present study, we will follow the recommendations of Julious et al., who support that 12 subjects per group are enough for pilot clinical trials [33, 34].

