### Statistical analyses

All analyses will be conducted intention-to-treat by a statistician blinded to group allocation. Descriptive analyses will be used as mean and standard deviation for parametric data and median and interquartile interval for non-parametric data. The analysis will include examining data distribution and variance equality to confirm the appropriate application of parametric analysis. Information from the latest available evaluation will be used for missed sessions. Two-way analyses of variance with repeated measures at the three-time points (baseline, post-intervention, and follow-up) will be implemented for all parametric outcomes to determine the statistical significance of the between-group differences and reported as mean differences between groups (95% CI) [35]. For non-parametric outcomes, the Kruskal–Wallis test will be used to determine the statistical significance of the between-group differences and reported as mean differences between groups (95% CI) [35]. Baseline characteristics judged clinically different between groups may be included as covariates and will be analysed using analysis of covariance (ANCOVA) and presented as mean differences between groups (95% CI) [35]. All analyses will be performed using the SPSS software (23.0 version).

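### Outcomes judged non-parametric are tested by ranks but reported as mean differences with a 95% CI, which the test does not estimate, and no outcome is assigned to a route in advance

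*Protocol article*

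**What the plan says.** All statements are in the protocol article.

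- **Choice of route** (Statistical analyses): "The analysis will include examining data distribution and variance equality to confirm the appropriate application of parametric analysis". No criterion is given, and no outcome is named as belonging to either route.
- **Parametric route** (same section): "Two-way analyses of variance with repeated measures at the three-time points (baseline, post-intervention, and follow-up) will be implemented for all parametric outcomes", reported as mean differences with 95% CI.
- **Non-parametric route** (same section): "For non-parametric outcomes, the Kruskal–Wallis test will be used to determine the statistical significance of the between-group differences and reported as mean differences", again with a 95% CI. The Methods paragraph of the abstract says the same: "the Kruskal–Wallis test for non-parametric outcomes will be used to determine the statistical significance of the between-group differences and reported as mean differences".
- **Description** (Statistical analyses): "median and interquartile interval for non-parametric data"; means and standard deviations are kept for parametric data.
- **Size** (Sample size estimate; abstract): "12 subjects per group are enough for pilot clinical trials", and "A total of 24 participants will be recruited".
- **Purpose** (Background): the trial is to supply a power analysis for Phase III. The sample size section says that the mean and SD needed for such a calculation are not available in the literature.

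**The concern.** An outcome on the non-parametric route is described by its median, tested on its ranks and reported as a difference in means. These are three different summaries. The CI must come from a method that the article does not name, and the obvious candidate, a t-type interval, leans on the distributional assumption that has just been set aside.

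Two features of the route add to this. It is chosen from the trial's own data, so the analysis of the primary outcome stays open until those data have been seen. And Kruskal–Wallis compares independent groups on one value per person, so it does not model the three visits that the parametric outcomes get. Outcomes on the two routes would not answer the same question.

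At stake is the reading of the pilot. The Discussion makes the next phase depend on whether the program appears beneficial. If the p-value and the CI point different ways, that word has no single meaning for the outcome concerned.

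**Working it through.** **1. Size.** 2 arms × 12 = 24, as stated. There is no power calculation to reproduce.

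**2. What the test estimates.** For groups with rank sums R₁ and R₂, N = n₁ + n₂ and no ties,

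H = 12 / [N(N + 1)] × (R₁²/n₁ + R₂²/n₂) − 3(N + 1).

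With two groups, H is the square of the standardised Mann–Whitney statistic. In a check with 12 per arm, both tests gave p = 0.2253 (no continuity correction). Only ranks enter, so no mean difference or CI for one can come out.

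**3. An example of conflict (invented data, 12 per arm).** Control: 1, 2, …, 11, 80. Experimental: 6.5, 7.5, …, 17.5.

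- Rank sums are 105 and 195. H = 12/(24 × 25) × (105²/12 + 195²/12) − 75 = 0.02 × 4087.5 − 75 = 6.75, p = 0.009.
- Mean difference: 12.00 − 12.17 = −0.17, Welch 95% CI −14.0 to 13.7.
- Hodges–Lehmann shift (median of the 144 pairwise differences): +5.5. For its CI, 72 − 1.96 × √(144 × 25/12) = 38.05, so the 38th smallest and 38th largest differences give 1.5 to 8.5.

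Under the plan's wording, p = 0.009 would stand beside −0.17 (−14.0 to 13.7). The shift and its CI agree with the test. The example shows that conflict is possible, not how often it occurs.

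**4. How often they disagree.** Simulations with 12 per arm compared Kruskal–Wallis at p < 0.05 with whether a 95% CI for the mean difference excludes zero. The protocol states no significance level; 5% is assumed to match the 95% CI. The distributions are also assumptions.

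| Assumed data | Shift | Disagree |
|---|---|---|
| Log-normal, σ 0.5 / 0.75 / 1.0 | none | 2.6% / 3.4% / 3.9% |
| Normal | 1 SD | 6% |
| Log-normal, σ 0.5 | 0.375 (log scale) | 10% |
| Log-normal, σ 0.8 | 0.6 | 14.7% (15.7% in a repeat with the Welch interval) |
| Log-normal, σ 0.5 | 0.5 | 10.9% |
| Log-normal, σ 0.75 | 0.75 | 17.9% |
| Log-normal, σ 1.0 | 1.0 | 26.8% |

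The rank test has about 41% power in the rows with shifts 0.375 and 0.6, and about 63% in the last three. With 10,000 runs, the Monte Carlo standard error at 15% is √(0.15 × 0.85/10,000) = 0.4 percentage points.

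**5. Choice of route.** The protocol names no check. If it were a Shapiro–Wilk test at 5% on each arm of 12, it would flag log-normal data in 30% (σ 0.5), 52% (σ 0.75) and 71% (σ 1.0) of samples. It would flag at least one of two truly normal arms in 9%. If both arms were pooled to 24 values, detection at σ 0.5 would rise to about 61%. These figures only illustrate what a data-led choice may involve at this size.

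**The case against.** **Pilot status.** This is a 24-person pilot without a formal sample size. Its Discussion urges caution and rules out a change in practice. Phase III planning needs a mean difference and an SD, so reporting means serves that purpose, and the rank p-value does not feed it. This stands and lowers the weight. It does not make the stated pairing coherent, and it is a reason to keep the mean difference and give it a named method.

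**Condensed article.** Details of a distribution check are commonly left to an analysis plan, and the statistician is blinded to allocation. Both points stand: the missing criterion alone would be no finding, and blinding limits deliberate selection. But the article itself states the mismatched pairing, twice, and blinding does not stop the data from deciding the route.

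**Frequency of conflict.** It depends on the scenario, and the document gives no outcome's distribution. This stands, so only a range can be given.

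Stronger readings that a reader might infer, and that the document does not support:

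- *The rank test costs substantial power.* With normal data, a 1 SD effect and a baseline correlation of 0.6, power was 64% for Kruskal–Wallis, 65% for an unadjusted t-test, 73% for Kruskal–Wallis on change scores and 81% for ANCOVA. Almost all of the gap comes from baseline adjustment, not ranks. ANCOVA is not the plan's default parametric route either, and the article does not say whether ranks are taken of post values or of changes.
- *Kruskal–Wallis will be run across the three visits as if they were independent.* The article ties the test to differences between groups, so this is conjecture.
- *A weak normality test will pick the analysis largely by chance.* No such test is named.

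**Conclusion.** The concern holds in this form: the rank test and the reported estimate do not belong together, the descriptive summary fits neither the mean difference nor its CI, and the route is left to the trial's data for every outcome, daily steps included. This follows from the article's wording and needs no simulation.

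The practical size is uncertain. Test and CI disagree on significance in about 3% of trials with no effect, 10 to 16% with moderate log-normal skew where the rank test has about 40% power, and up to 27% with strong skew and a larger shift. These figures assume 12 complete values per arm, a 5% level, log-normal data and a t-type interval, none of which the article fixes except the 12.

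Severity is moderate. The fault affects only outcomes sent down the rank route, and it does not invalidate the trial.

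**What to change.** In Statistical analyses, and to match in the abstract:

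1. Name one analysis for each outcome before data are seen, starting with daily steps, and drop the choice of test by inspection.
2. Preferably use a mean difference from a single pre-specified model for all continuous and score outcomes, with a bootstrap or permutation CI where skew is a concern. Report means and SDs for all of them, with medians added if wanted. This also supplies the figures needed to plan Phase III.
3. If a rank test is kept, call it Mann–Whitney, state whether it is run per visit or on change from baseline, and report the Hodges–Lehmann shift with its CI in place of the mean difference.

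The least repair would be to name the method behind the CI. That removes the gap in the text but leaves a p-value and a CI that can conflict, so item 2 or 3 is better.

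The cost is a change of wording and some analysis code. Sample size, visits and data collection do not change.

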## Methods

### Design

A prospective, pragmatic, two-arm, parallel-group, Phase II pilot randomised clinical trial with concealed allocation, allocation ratio (1:1), blinded measurement, and intention-to-treat analyses will be carried out. The study was approved by the Federal University of Minas Gerais Ethics Board (65672517.6.0000.5149) Hospital Ethics Board (17/2017) and registered on clinicaltrials.gov on 4^th^ April 2022 (NCT05461976). Any modifications that may occur during this trial will be reported in clinicaltrials.gov.

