### Primary outcome

A triaxial accelerometer will measure physical activity (Actigraph wGT3X-BT, Pensacola, FL, USA) [23]. Participants will be asked to wear the device on their waists and non-paretic sides [1]. They will be advised to wear the device during waking hours, except during water activities. The mean of steps taken per day over four days (two weekdays and two weekend days) will be recorded and reported in baseline (week 0), post-intervention (week 12) and follow-up (week 24) in both experimental and control groups. The mean of daily steps will be analysed to compare groups after intervention. As a way to describe the sample, the percentage of time spent in sedentary activities and moderate and vigorous physical activity will be reported at baseline, post-intervention, and follow-up in both groups. These data will not be used to compare groups after intervention. The Actigraph shows adequate psychometric properties in individuals after a stroke [23].

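### Covariates may be picked by observed baseline imbalance, with no threshold, and the plan does not say whether the resulting ANCOVA or the repeated-measures ANOVA is the main result

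*Protocol article*

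**What the plan says.** The default model in the Statistical analyses section is firm: "Two-way analyses of variance with repeated measures at the three-time points (baseline, post-intervention, and follow-up) will be implemented for all parametric outcomes". Its purpose is "to determine the statistical significance of the between-group differences and reported as mean differences between groups (95% CI"). Mean daily steps, the primary outcome, falls under it if judged parametric, and the Primary outcome section adds: "The mean of daily steps will be analysed to compare groups after intervention".

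The covariate rule follows: "Baseline characteristics judged clinically different between groups may be included as covariates and will be analysed using analysis of covariance (ANCOVA"). Its results are to be "presented as mean differences between groups (95% CI"), the same form of report as the ANOVA. The section does not:

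- list any covariate;
- define how large a difference counts;
- say who judges it, or whether this happens before outcome data are seen;
- say whether the ANCOVA replaces the ANOVA, stands beside it or is a sensitivity analysis.

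The Methods part of the Abstract mentions only the ANOVA and the Kruskal–Wallis test. The one related safeguard is that the statistician is blinded to allocation.

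On size, the Sample size estimate section relies on a recommendation that "12 subjects per group are enough for pilot clinical trials", and the Abstract states: "A total of 24 participants will be recruited".

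**The concern.** Allocation is random, so a difference between the arms at baseline is chance, whatever its size. Adjustment earns its place when a variable predicts the outcome, because it then removes noise and corrects for whatever chance imbalance occurred. Selecting on imbalance ignores prognostic strength. A weak predictor that looks unbalanced gets in, and a strong one that looks balanced stays out. Baseline steps, the obvious predictor of later steps, would be a covariate only if the arms happened to differ on it.

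The permissive verb adds a second problem. Once baseline data are in, there may be an ANOVA and one or more ANCOVAs, each with its own difference, interval and p-value, and no stated order among them. The trial exists to supply estimates for planning a Phase III trial, and the Discussion makes that next step depend on whether the programme looks beneficial. Both the estimate and its variance would then depend on an undocumented choice.

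**Working it through.** **Inputs.** 12 per arm (Sample size estimate); 1:1 allocation (Design). No significance level is stated, so two-sided 0.05 is read from the 95% intervals. The plan's own figure reproduces: 2 × 12 = 24. It states no power, effect size or SD, so there is no power formula to test.

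**How often the rule could be triggered.** For a standardised baseline measure, the difference between arm means has standard error √(2/12) = 1/√6 SD. The chance that one measure differs by at least *t* SD is 2[1 − Φ(*t*√6)]; for at least one of *k* independent measures it is 1 − (1 − *p*)^*k*. The outcome sections give 11 baseline measures: steps, body mass index, waist, blood pressure, depressive symptoms, 6-minute walk, habitual speed, maximum speed, self-efficacy, participation and quality of life.

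| Assumed threshold | One measure | At least one of 11 |
|---|---|---|
| 0.5 SD | 22% | 94% |
| 0.8 SD | 5.0% | 43% |
| 1.0 SD | 1.4% | 15% |

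The last column is too high to the extent that the measures are correlated, as body mass index and waist, or the three walking measures, surely are. With 5 independent measures at 0.5 SD it is 71%.

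**How far the estimate can move.** Adjusting for a covariate that is out of balance by 0.5 SD moves the estimated difference by about 0.5 × *r* SD, where *r* is its correlation with the outcome. For an assumed *r* of 0.3 to 0.7 this is 0.5 × 0.3 = 0.15 SD to 0.5 × 0.7 = 0.35 SD.

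**Error rate with no true effect (simulation).** 12 per arm, independent normal covariates, a linear model for one post-intervention measure, nominal two-sided 5%. This stands in for the planned repeated-measures ANOVA; it does not reproduce it.

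| Policy | Simulated error |
|---|---|
| Never adjust | 5.0-5.1% |
| One pre-specified covariate, always included | 5.0-5.1% |
| Every covariate beyond 0.5 SD, always included | 1.5-4.1% |
| More favourable of unadjusted and fully adjusted, 0.5 SD | 5.6-6.4% |

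These rows use 40,000 trials per scenario, with 1, 5 or 8 covariates and correlations of 0.2 to 0.6 with the outcome. With stricter thresholds the always-included rule moves back towards 5%, so about 2-5% describes it overall.

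The most favourable of all models allowed by the threshold was simulated with 6 covariates and 4,000 trials per scenario (Monte Carlo error about 0.4 points):

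| Threshold | Error, correlations 0.1 to 0.35 |
|---|---|
| 0.5 SD | 6.9-9.1% |
| 0.8 SD | 5.7-6.1% |
| 1.0 SD | 4.6-5.8% |

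A correlation of 0.35 for each of six independent covariates implies a joint R² of 6 × 0.35² = 0.735, which is very high. At 0.2 it is 6 × 0.2² = 0.24, and the error at 0.5 SD was 7.9%.

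**Why the two directions differ.** If imbalance always triggers adjustment, the chance shifts that would have produced false positives are removed, while the trials left unadjusted keep a standard error that is too large for their good balance. The test is then conservative. Inflation arises only when the option is used selectively.

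**The case against.** Several stronger readings are tempting, and the text does not carry them.

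- A reader might infer that the primary model is picked from the data, with ANCOVA displacing ANOVA. The ANOVA is stated as something that will be done, and nothing says the ANCOVA replaces it. What stands is that the ANCOVA's status is left open.
- A reader might infer that the outcome's baseline is ignored. It is one of the three time points in the ANOVA. That is not covariate adjustment, but it is not neglect.
- A reader might infer that imbalance is near certain at this size. That holds at 0.5 SD with many independent measures and fails at stricter readings of a clinical difference.
- A reader might infer that false positives are always inflated. Followed mechanically, the rule does the opposite, and the higher figures assume the most favourable result is always the one reported.

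The statistician is blinded to allocation. This limits steering towards a known arm. It does not prevent choosing the model with the smaller p-value, which needs no knowledge of which arm is which, and the plan does not say that covariates are fixed before outcomes are seen.

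Finally, this is a 24-person pilot with no stated significance level, and its Discussion says that results need caution and cannot change practice. That lowers the weight of any error-rate argument. It does not remove the point, because significance tests are planned and the estimates are meant to inform Phase III.

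**Conclusion.** The point holds in a limited form. The plan states a poor rule and does not merely leave a detail to another document: covariates enter by judged imbalance, optionally and without a threshold, and the standing of the resulting ANCOVA is undefined. At nominal 5%, the simulated error runs from about 2-5% if the rule is always applied to about 8% if the more favourable model is reported at a 0.5 SD threshold, and only 5-6% at 0.8-1.0 SD. These figures rest on an assumed threshold, independent normal covariates, assumed correlations with the outcome and a single post-intervention measure.

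The stronger ground for change is the criterion itself. It selects on chance and leaves adjustment for baseline steps to luck. The change is worth making because it is nearly free; the practical weight in a pilot is moderate.

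**What to change.** For outcomes analysed parametrically:

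1. Make the main between-group estimate at Week 12, and likewise at Week 24, an ANCOVA or a repeated-measures model of the post-baseline values. Include the outcome's own baseline value as a covariate regardless of observed balance.
2. Remove baseline from the response levels of that model, since it cannot be both a response and a covariate.
3. Name any further covariate now, on prognostic grounds, and always include it.
4. Label any adjustment prompted by observed imbalance as a sensitivity analysis.

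Outcomes analysed by Kruskal–Wallis are outside this change, because that test takes no covariate.

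The baseline values are already collected. The cost is one degree of freedom per covariate: with 24 participants and a single time point, residual degrees of freedom go from 24 − 2 = 22 to 24 − 3 = 21 for the baseline value. The Statistical analyses section and the Methods part of the Abstract need matching edits, because both currently describe the ANOVA.

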## Discussion

Although self-management programs have been used to promote physical activity after stroke, the effectiveness of this strategy is still unclear [5, 6]. In this way, further studies in the area are required [4, 7, 8]. Recently, we demonstrated, in a Phase I study, the feasibility of implementing a home-based self-management exercise program to promote physical activity among sedentary stroke survivors with mild walking disability in Brazil [1]. In conclusion, our feasibility study showed that a Phase II study is required. However, some barriers to implementing the next phase were found in this previous study (i.e. lack of medical clearance for participants to practice physical activity, too much time spent in the data collection section, difficulty in acquiring information about exercise adherence, etc.). Therefore, in the present Phase II study, we will address these previously encountered barriers and, in addition, test this program against a control group. If beneficial, the results of this study will provide data to plan a fully powered future Phase III clinical trial aimed at verifying the program’s efficacy in promoting physical activity after stroke.

This study has some limitations. First, since a sample size calculation will not be made, the interpretation of results must be taken with caution. Second, this is a Phase II trial, which aims to determine whether an intervention has potential benefits to justify further investigation in a Phase III trial [36]. Thus, the results from the present study cannot be used to change clinical practice [36]. For this, more investigation is necessary in the next trial phase. The strengths of the present study are that if beneficial, we will provide data to plan a fully powered future Phase III trial. Besides, we will raise barriers to implementing the intervention in the next Phase, which can increase the probability of success in a future study. If not beneficial, we will avoid spending time and expenses on a large study.

